#### 3.1.5. Supporting Administrative Data for Effectiveness Evaluation

Extensive administrative data are being used to support the effectiveness evaluation of the FPR. The connection form (i.e., referral document) and its attachments (such as family violence screening tools, diagnoses of disabilities, prior OOHC history of parent and so on) provide detailed information to support our understanding of parental context, connection to services and culture, and existing safety concerns. The closure checklist, which is completed by the key worker, also provides information about the service and education connection and participation.

### 3.2. Outcome Measures for Objective 2–Implementation

Table 1 describes the implementation processes that MacKillop Family Services are evaluating, the data it is using, and how it is being sourced. Much of these data are qualitative and sourced directly from MacKillop Family Services staff. Being respectful of the workload and time pressures faced by the key workers, they are only being engaged every six months in a focus group during a regularly planned team meeting. This will ensure that their capacity to keep families as their focus is not compromised. Approximately five key workers from each of the nine teams will participate in the focus group, totalling a possible sample size of 45 participants. The nine team leaders are interviewed every fortnight for 30 min to understand the immediate pressures and issues that their teams are facing, while their managers are interviewed every quarter.

#### 3.2.1. Acceptability, Appropriateness and Feasibility

Acceptability, appropriateness and feasibility is being assessed using qualitative methods at both the parent and staff levels. While validated measures for these factors exist, including the Acceptability of Intervention Measure (AIM), Intervention Appropriateness Measure (IAM) and Feasibility of Intervention Measure (FIM) [38], the considerable number of measures for parents and the key workers being time poor, make their use infeasible despite their brevity. This decision was made in conjunction with MacKillop staff.

#### 3.2.2. Fidelity

Implementation fidelity is being measured, relating to the connection, assessments, information sharing, adherence and quality. Parent readiness and the program reach is also being examined. Much of the data are sourced through case notes, presence of certain documents in the case file and routine reporting.

#### 3.2.3. Readiness and Reach

Readiness is assessed through the connection form (i.e., referral form obtained from child protection), case notes and the first PEEM completed by parents at baseline. The PEEM offers a snapshot of parent reflexivity and understanding of their parenting practices. For example, if parents score themselves 9 or 10 for most questions, this suggests that they may not be ready to undertake work on their parenting skills. Program reach is determined by the number of clients who participated fully in comparison to the number who refused service.

#### 3.2.4. Process, Barriers and Enablers

The Consolidated Framework for Implementation Research [39] has five domains (Intervention, Outer Setting, Inner Setting, Individuals, and Process) to guide the analysis of the qualitative data as barriers and enablers are identified. These factors will be examined through the lens of the implementation cycle [8], which states that implementation takes between two to four years to do, each with stages. As such, some factors will not be relevant in the early stages compared to later stages. An examination of the process, barriers and enablers as they emerge is critical for MacKillop Family Services to actively respond and manage barriers as they arise.

#### 3.2.5. Parent Trauma History

Parental trauma history will be examined in two ways: (1) examination of connection documentation for personal OOHC experience; and (2) through the Adverse Childhood Experiences (ACEs) survey [40]. The connection documentation is the referral form which is provided by child protection to MacKillop Family Services before the family is accepted into the program. This form indicates numerous demographic characteristics regarding the parents, including whether they have had personal OOHC experience. The ACEs survey comprises seven categories of abuse or dysfunction, each with one or more questions; three categories are about childhood abuse that could be either psychological, physical or sexual; and four categories of household dysfunction including exposure to substance abuse, mental illness, violence towards a caregiver and criminal behaviour. Responses are scored as yes/no and adult respondents are asked to think about any time up until they were 18 years of age. The ACEs survey is completed on one occasion (towards the end of program engagement) with the FPR worker.

## 4. Analytical Considerations

The primary quantitative outcome of this study is to examine the degree to which there are improvements in psychosocial outcomes among families who engage in the program. All completed questionnaires will be de-identified by a specific data aggregation worker who will assign a unique ID code (e.g., FPR003) to each family so that their data remain anonymous to the research team. Descriptive statistics will be calculated based on administrative and demographic data sourced from the referral form. Main caregiver complexity will be determined using the ACEs survey and the number of ACEs will be calculated. A series of paired sample t-tests (repeated measures) will be used to compare participants’ mean differences on the measures at the beginning and end of the program. Analysis of Variance will be employed to review the number of reports before, during and after the program to determine any statistical differences. The number of care episodes and time to reunification will be analysed descriptively. All analyses will be performed using the Statistical Package for the Social Sciences (SPSS) software.

All qualitative data will be analysed using thematic analysis [41]. Data collection and analysis will occur concurrently so that data saturation can be adequately assessed. All audio recordings will be transcribed verbatim and systematically coded. Following in-depth review of the coded data, independent themes will be identified and developed based on recurrent content reflecting the different aspects of program implementation. The process of refining and reviewing themes will be an iterative process until themes are representative of the most pertinent and recurrent aspects of the data.

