### 2.3. Participants

There are two participant groups in this study: parents and MacKillop Family Services staff.

Parents: Parents either have children (0–17 years of age) who are vulnerable to removal from the home due to a child protection assessment of risk, have children already in OOHC, or are pregnant and have had ‘unborn’ reports to child protection. These parents may have multiple factors that are contributing to their risk profile including recent family violence, drug or alcohol misuse, fragile mental health, court orders and justice involvement among others. Parents can vary in age and may be adolescent parents or those who are currently living in a care arrangement (foster, kinship, or residential OOHC). Sample size calculations have been conducted using G*Power based on the NCFAS as this measure goes across most efficacy outcomes. For an analysis of variance test with the alpha set at 0.005, correlations between repeated measures set at 0.50 and power of 0.95, a total sample of 98 families will be required. To allow for a 25% rate of non-completion, at least 123 families will be recruited. During the study period, it is expected that up to 1100 families will engage in MacKillop’s FPR program. Based on similar research, we expect a high number of families to consent to participate in the study [25], therefore, it is expected that this sample size requirement will be met by the end of the study period.

MacKillop Family Services Staff: MacKillop directors, managers, team leaders and practitioners involved in the delivery of the FPR program are eligible to participate in interviews or focus groups about their experiences of implementing the program. Only staff who consent will take part in the research evaluation.

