## 5. Discussion

This paper describes the protocol of a hybrid style, implementation and outcomes study using a pre-post design with selected follow-up data and qualitative data. The study will serve two key purposes. First, it will seek to demonstrate the extent to which the Response is effective in improving outcomes for families and children following the program. Whilst this is not a randomised controlled trial, the pre-post design will allow some conclusions to be made about the potential impact of the program on engaged families. In turn, this will develop the Response’s evidence base and provide new knowledge about the implementation of intensive family services more broadly. Second, the findings of this study, particularly the implementation findings, will help inform future iterations of the program. It is intended that key program components, processes, or operational issues may be adapted, refined, or remedied to improve implementation and uptake of the Response. Therefore, the evaluation will help ensure that the program is trialled, tested, and adapted accordingly to effectively meet the complex and unique needs of some of the most vulnerable families in the Victorian community.

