## 6. Conclusions

The current study is necessary and critical for generating Australian evidence regarding the effectiveness of an intensive family service program that aims to preserve or reunify families through the provision of assertive outreach support. Importantly, if the program is found to be well-implemented and yields significant improvements in families’ outcomes from baseline to closure, then this would provide strong support for the scale-up and dissemination of the Response across Australia. In turn, this could begin to foster the intergenerational outcomes that many of the target families currently experience.

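### The primary outcome is an aim with no named score or test level, and the scale-up claim goes further than a single-group pre-post design allows

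*Protocol article*

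**What the plan says.** - **Primary outcome (Section 4, Analytical Considerations).** "The primary quantitative outcome of this study is to examine the degree to which there are improvements in psychosocial outcomes among families". No instrument, domain, score or time point follows.
- **Sizing (Section 2.3).** The calculation is "based on the NCFAS as this measure goes across most efficacy outcomes". Its inputs are given as "For an analysis of variance test with the alpha set at 0.005, correlations between repeated measures set at 0.50 and power of 0.95", leading to 98 families, or 123 after an allowance for non-completion. The NCFAS is not called primary, the domain or score is not identified, and no effect size is given.
- **NCFAS-GR (Section 3.1.1).** It has ten domains, is rated by the FPR worker, and is completed at the start, around the middle and at closure.
- **Analysis (Section 4).** The measures are compared between the beginning and end of the program by a series of paired t-tests. Analysis of variance is assigned only to the number of reports before, during and after the program. No significance level or order of testing is given.
- **Design (Section 2.2).** A single group measured before and after, with stated reasons for having no control group and an acknowledgement that this has limitations.
- **Interpretation.** Section 5 says "the pre-post design will allow some conclusions to be made about the potential impact of the program on engaged families". Section 6 says that if the program is well implemented and produces significant improvements, "then this would provide strong support for the scale-up and dissemination of the Response across Australia". The abstract makes the same link without the implementation condition.

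**The concern.** Three statements that should fit together do not. The declared primary outcome cannot be computed, because it is not a variable. The one significance level in the article belongs to the sample size calculation and is not linked to any test in the analysis section. The strongest conclusion in the article is tied to significance on outcomes that are neither named nor ranked.

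Followed as written, the plan leaves the choice of what counts as the main result until the data are in. It also permits a recommendation that the design cannot carry. Families enter when a child is at risk of removal or already removed, so some improvement by closure may occur without the program. The NCFAS is scored by the worker who delivers the service. Consent is expected in months two to four at worker discretion (Section 2.4), which may favour engaged families. A significant pre-post change cannot be separated from these influences.

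**Working it through.** **1. The plan's own figure.** The sample of 98 cannot be reproduced from the stated inputs, because no effect size is given. Assume a within-subject repeated-measures ANOVA with sphericity:

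λ = f²·N·m/(1 − ρ), df1 = m − 1, df2 = (N − 1)(m − 1), with ρ = 0.50 and power 0.95.

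| Occasions m | Alpha | Assumed f | N |
|---|---|---|---|
| 3 | 0.005 | 0.15 | 172 |
| 3 | 0.005 | 0.20 | 98 |
| 3 | 0.005 | 0.25 | 64 |
| 3 | 0.05 | 0.20 | 66 |
| 2 | 0.005 | 0.23 (paired dz = 0.46) | 98 |

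With f = 0.20 and the three NCFAS occasions, λ = 0.04 × 98 × 3/0.50 = 23.52 and the result is exactly 98. On that assumption 0.005 was the level used and is not a misprint of 0.05. With two occasions the F test is equivalent to a two-sided paired t-test, and 98 corresponds to dz = 0.46. The article does not say which was intended.

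**2. Where 0.005 may come from.** 0.05/10 = 0.005, which fits the ten NCFAS-GR domains. The article does not make this link, so it is an inference.

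**3. How many tests the plan could involve.** The article gives no count. From the measures it describes:

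- One score each for NCFAS, PEEM, ASQ, SDQ, CBCL and BSI, plus reports: 6 + 1 = 7.
- Ten NCFAS domains, two combined CBCL scales, one score each for PEEM, ASQ, SDQ and BSI, plus reports: 10 + 2 + 4 + 1 = 17.
- All scales: NCFAS 10 + 1 attachment indicator, PEEM 1, ASQ 1, SDQ 1, CBCL 8 + 2, BSI 9, reports 1 = 34.

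**4. Chance of at least one false positive**, all nulls true and tests independent: 1 − (1 − α)^k.

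| Tests k | α = 0.05 | α = 0.005 |
|---|---|---|
| 7 | 30% | 3.4% |
| 10 (NCFAS domains only) | 40% | 4.9% |
| 17 | 58% | 8% |
| 34 | 83% | 16% |

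Independence does not hold. The two combined CBCL scales, for example, are built from the syndrome scales (Section 3.1.2). The figures are therefore upper guides.

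**5. The interpretive statements side by side.** Section 2.2 concedes the limits of having no control group. Section 5 confines itself to some conclusions about potential impact. The abstract and Section 6 move from significance to strong support for national scale-up. The last pair goes further than the first two, and no analysis detail held elsewhere would reconcile them.

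**The case against.** The strongest reply is that most of this is silence, not error. A journal article commonly leaves test levels and adjustment to a fuller document, which is not shown, and 0.005 suggests that multiplicity was considered. That stands: a missing multiplicity rule alone would not be a finding. What remains is that the article does declare a primary outcome, and states it as an aim. It also gives a strict level without saying which tests it governs.

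Two stronger readings are tempting.

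- **Any one significant result among more than 30 tests would count as success.** The documents do not say this. Section 6 speaks of improvements in the plural and adds good implementation, and it is a closing remark with no decision rule. A count above 30 requires every CBCL and BSI scale to be tested separately, which is nowhere stated. The 0.05 level is not stated either. If only improvements count, each test contributes about 0.025, and the chance of at least one falls to 1 − 0.975^7 = 16% for 7 tests and 1 − 0.975^34 = 58% for 34.
- **Regression to the mean alone would exceed the detectable effect.** Taking ρ = 0.50, a group 1 SD below the population mean would be expected to move (1 − 0.50) × 1 = 0.5 SD, above 0.46. But the 1 SD has no source. A 0.5 SD deviation gives only 0.25 SD, and the threshold is passed only beyond 0.46/0.50 = 0.92 SD. The ρ is also a planning value for enrolled families, not for an unselected population. The direction is plausible; the size cannot be computed from the documents.

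The missing control group is disclosed and justified in Section 2.2. The criticism is of the conclusion drawn, not of the choice of design.

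**Conclusion.** The point holds in a limited form and should be addressed. The primary outcome is not a named score and time point. The sizing level of 0.005 is not tied to any planned test. The abstract and Section 6 claim more than a single-group pre-post design, or the article's own Discussion, allows.

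The multiplicity exposure is a range: 30% to 83% at 0.05 and 3% to 16% at 0.005, for 7 to 34 tests. It rests on independence and on all nulls being true, so it is an upper guide. It should not be read as the probability that the study is declared a success by chance, since no success rule exists. Regression to the mean after a crisis-driven referral could add to any observed change by an amount that cannot be computed here.

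**What to change.** 1. In Section 4, name baseline-to-closure change in each of the ten NCFAS-GR domains as primary. Test the ten with Holm's procedure at family-wise 0.05. The first step is 0.005, consistent with the sizing level; if that was the reason for 0.005, say so in Section 2.3.
2. Label all other measures secondary, including the attachment indicator and the number of reports. Give estimates with 95% confidence intervals.
3. Reword the abstract and Section 6 to agree with Section 5: a significant pre-post change is consistent with benefit and supports a controlled evaluation, but does not by itself give strong support for scale-up.

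**Cost.** No extra data and no change in sample size. Fewer results may be called significant, and the headline claim is weaker. Because the study is registered, naming the primary outcome is more than an editorial change: it should be made before outcome data are examined and notified to the ethics committee and registry, as Section 2 already provides for protocol changes.

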### 3.1. Outcome Measures for Objective 1–Effectiveness

#### 3.1.1. Parent and Family Focused Quantitative Measures

North Carolina Family Assessment Scale–for General Services and Reunification (NCFAS-GR) [26]:

The NCFAS-GR assesses change over time on ten family functioning domains that cover topics like safety, wellbeing, environment, and social life. The scale is completed by the FPR worker who accumulates knowledge about the family and then completes it in one sitting. Domain scores are measured using a six-point Likert scale ranging from “Serious Problem/Weakness = −3” to “Clear Strength = 2”. There is the option to provide a short comment to the score. The scores strongly guide the planning and practice, while also informing the child and family action plans and family goals. The NCFAS-GR is completed at the start of the program, after approximately 3 months or the middle, and upon closure. The NCFAS-GR has high internal consistency (*a* = 0.79–0.91) when implemented with families involved with Child Protection [27].

As per Figure 1, the NCFAS is being used to measure four of the five effectiveness objectives. The parental capability and self-sufficiency domains measure parent knowledge, parenting skills (i.e., sleep settling, developing routines, responding to cues, use of consequences etc) and parenting capability. The family safety and environment domains measure safety and security of the family’s home environment. Family interactions will be measured using the family interactions subscale of the NCFAS, which comprises eight items examining bonding with children, communication with children, expectations of children, relationship between parents/caregivers, support within the family, and family routines, rituals, and activities. The first three items provide an indicator of parent–child attachment, while the combination of all eight items yields an overall score of family interactions. The child wellbeing and family health domains examine the child’s health and development. In addition, the social life domain measures the child’s connection to education, as well as the parent’s connection to community services.

Parent Efficacy and Empowerment Measure (PEEM) [28]:

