## Figures and Tables

**Figure 1 ijerph-18-10279-f001:**
[figure not shown]
Outcomes and measures to evaluate the effectiveness and implementation of FPR. Note. NCFAS = North Carolina Family Assessment Scale; PEEM = Parent Efficacy and Empowerment Measure; MARAM = Family Violence Multi-Agency Risk Assessment and Management Framework; ASQ = Ages and Stages Questionnaire; SDQ = Strengths and Difficulties Questionnaire; CBCL = Child Behaviour Check List; BSI = Brief Symptom Inventory.

**Table 1 ijerph-18-10279-t001:** Effectiveness and implementation outcome measures.

Outcome	Individual Measures	How Measured	When Measured
	Program Effectiveness Outcomes		
Parental knowledge, skills, and confidence	Self-efficacy and empowerment Parenting capability and self-sufficiency	Connection form—parent strengths and capacity section; PEEM; NCFAS-parental capability and self-sufficiency subscales	NCFAS at baseline, mid and closure; PEEM at baseline and closure
Family safety and home environment	Recent family violence screens (MARAM) Child protection notifications OOHC entry/re-entry	Connection form NCFAS—family safety subscale, environment subscale MARAM—intermediate screen Linked data from the Victorian Government	NCFAS at baseline, mid and closure; MARAM at intake
Child development (early years) or behavior (adolescence), relationships and education	Looking at changes in child development over time Is there a good parent/child relationship What is the child’s connection to education	NCFAS—Child Wellbeing, Family health subscales, Family interactions; ASQ—Child development up to 60 months SDQ—Adolescent Behaviour (regional) CBCL—Adolescent Behaviour (metro) BSI—Adolescent Behaviour (metro) Connection form; Closure checklist; Closure goals; Client interviews and exit survey	NCFAS at baseline, mid and closure. Others at intake and closure
Connection to services and culture	Are Aboriginal and Torres Strait Islander families supported in their cultural connection.	Connection form; NCFAS—social life subscale; Closure checklist; Cultural support plan of Aboriginal and Torres Strait Islander children are provided; Families are connected to cultural communities; Staff have cultural training and access to a cultural advisor	NCFAS at baseline, mid and closure. Baseline for connection form; and closure for closure checklist

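### The 98 families and 0.95 power rest on an ANOVA of the NCFAS, but the stated NCFAS analysis is a baseline-to-closure paired t-test that leaves out the mid-programme score

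*Protocol article*

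**What the plan says.** Section 2.3 (Participants) bases the sample size on the NCFAS and describes the calculation thus: "For an analysis of variance test with the alpha set at 0.005, correlations between repeated measures set at 0.50 and power of 0.95". The result is 98 families, raised to at least 123 for 25% non-completion. Neither the effect size nor the number of repeated measurements entered is stated.

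Section 3.1.1 sets the measurement schedule: "The NCFAS-GR is completed at the start of the program, after approximately 3 months or the middle, and upon closure". Table 1 repeats it: "NCFAS at baseline, mid and closure".

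Section 4 (Analytical Considerations) plans a series of paired t-tests on "mean differences on the measures at the beginning and end of the program". The only analysis of variance it describes is for the number of child protection reports before, during and after the programme. It names no alpha. The abstract mentions F tests alongside the t-tests but does not say which outcomes they serve.

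**The concern.** The test that justifies the sample size is not the test that section 4 assigns to the measure it was sized on. Two things follow.

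First, a reader cannot tell what power the planned NCFAS comparison has. An omnibus test over several occasions and a single before-after contrast respond differently to the same pattern of change.

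Second, a paired t-test uses only families with both a baseline and a closure score. The mid-programme score plays no part, even for a family that has a baseline and a mid score but no closure score. If families who are doing less well by mid-programme are more likely to lack a closure score, the average change among completers overstates the programme's effect. There is no control group (section 2.2), and the Conclusions tie support for scale-up to significant improvement from baseline to closure. This change score therefore carries much of the effectiveness evidence.

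**Working it through.** **Inputs from the protocol.** Alpha 0.005, correlation between repeated measures 0.50, power 0.95, N = 98 and 25% non-completion (section 2.3); NCFAS at three occasions (section 3.1.1, Table 1). **Not stated:** effect size f, number of occasions m, sidedness. These are assumptions below.

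**1. Reproducing 98.** For a one-group within-factor F test, λ = f²·N·m/(1 − ρ), df1 = m − 1, df2 = (N − 1)(m − 1), sphericity assumed.

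| m | f | N for power 0.95 at alpha 0.005 |
|---|---|---|
| 3 | 0.15 | 172 |
| 3 | 0.20 | 98 |
| 3 | 0.25 | 64 |
| 2 | 0.20 | 128 |
| 2 | 0.25 | 84 |
| 2 | 0.2295 | 98 |

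For m = 3 and f = 0.20, λ = 0.04 × 98 × 3/0.5 = 23.5 and 98 is the smallest N that reaches 0.95. Three occasions at a round f of 0.20 is the most natural source, but it is back-solved. At alpha 0.05 the same inputs need only 66, so 0.005 does not look like a misprint.

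**2. Power of the planned paired t-test, if m = 3 and f = 0.20.** Here f is the SD of the occasion means divided by the within-occasion SD. The standardised change is dz = d/√(2(1 − ρ)), which equals d at ρ = 0.50.
- Linear change, means (0, d/2, d): SD of means = d/√6, so d = 0.20 × √6 = 0.490.
- All change in one interval, means (0, d, d) or (0, 0, d): SD of means = d√2/3, so d = 0.20 × 3/√2 = 0.424.

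Two-sided noncentral t at alpha 0.005:

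| Trajectory | dz | Power, 98 pairs | Power, 92 pairs | Pairs for 0.95 |
|---|---|---|---|---|
| Linear | 0.490 | 0.974 | 0.963 | 87 |
| One interval | 0.424 | 0.904 | 0.880 | 115 |

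The 92 is 123 × 0.75 = 92.25, rounded down.

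**3. If m = 2 was entered.** A two-occasion repeated-measures ANOVA is the paired t-test. With f = 0.2295, dz = 2 × 0.2295 = 0.459 and power with 98 pairs is 0.95. The power mismatch then disappears.

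**4. What 98 pairs support regardless of the reconstruction.** The smallest dz with 0.95 power at two-sided 0.005 is 0.459 for 98 pairs and 0.474 for 92 pairs.

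**5. Effect of selective loss (simulation).** Assumptions: three normal scores with unit SD and correlation 0.50, means 0, 0.245 and 0.49, and 25% of families without a closure score. The odds of loss rise by the stated ratio per SD less gain. The model column is a likelihood analysis using baseline and mid scores.

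| Loss depends on | Odds ratio | Completers' gain | Model estimate | Truth |
|---|---|---|---|---|
| Mid-programme gain (observed) | 2 | 0.57 | 0.49 | 0.49 |
| Mid-programme gain (observed) | 3 | 0.60 | 0.49 | 0.49 |
| Closure gain (unobserved) | 2 | 0.65 | 0.60 | 0.49 |
| Closure gain (unobserved) | 3 | 0.72 | 0.65 | 0.49 |

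The model removes the bias when loss depends on observed scores and only reduces it otherwise.

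**The case against.** Several points on the other side are sound.

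- **The question is a two-occasion one.** The abstract and Conclusions ask about change from intake to closure, and a paired t-test addresses that. This stands: the contrast is the right one. What can be improved is how it is estimated when closure scores are missing.
- **The study may not be short of power.** A reader might infer that it is underpowered, for instance power 0.86 with 98 families and 128 needed. That takes f = 0.20 on two occasions, which would not have produced 98. On the three-occasion reading, linear change gives the t-test more power than stated. The 123 is also a minimum, with up to 1,100 families expected in the programme. The documents do not support a claim of underpowering.
- **Non-completion is not the same as a missing closure score.** The worker completes the NCFAS, and Table 1 speaks of clients who closed early without saying that they lack one. A reader might infer that all 25% leave the analysis, but the protocol does not say how many do. A complete-case repeated-measures ANOVA would drop families with missing scores too, so restoring ANOVA alone would not help.
- **Loss of multiplicity control is not shown.** Alpha 0.005 equals 0.05/10 and there are ten NCFAS domains, so a reader might infer that testing at 0.05 gives a 40% chance of a false positive (1 − 0.95¹⁰ = 0.401). The protocol states no 0.05 for these tests, does not give this reason for 0.005, and one worker's ratings of one family are unlikely to be independent across domains. The figure should not be relied on.
- **The abstract's F tests might cover the NCFAS.** They name no outcome, and section 4 gives analysis of variance only to reports. The two places need to agree.

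**Conclusion.** The concern holds in a limited form. Section 2.3 attaches 98 families and 0.95 power to an analysis of variance of the NCFAS, and section 4 tests the NCFAS with a two-occasion paired t-test. The stated power is therefore not shown to be that of the planned test, and no stated analysis uses the mid-programme score.

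The direction of the power difference is open. It is about 0.97 or 0.90 instead of 0.95 on the inferred three-occasion reading with f = 0.20, and there is no difference if two occasions with f of about 0.23 were entered.

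The more practical consequence is the dropping of families without a closure score. Under 25% loss linked to mid-programme gain at an assumed odds ratio of 2 to 3 per SD, completers overstate a gain of 0.49 SD by 0.08 to 0.11 SD (0.57 − 0.49 and 0.60 − 0.49). The loss mechanism, its strength and the share of non-completers without a closure score are assumptions, not facts in the protocol. This should be fixed; it does not by itself invalidate the study.

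**What to change.** In section 4, analyse each NCFAS domain with a linear mixed model for repeated measures: baseline, mid and closure scores, time as a categorical factor, unstructured covariance, and all consenting families with any score. Take the baseline-to-closure contrast as the main estimate and test it at the sized alpha of 0.005. Keep the completers' paired t-test as a sensitivity analysis. State that the model removes bias only if loss depends on observed scores and otherwise only reduces it.

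In section 2.3, state the f and the number of occasions used, and restate the power for the one-degree-of-freedom contrast: 98 complete pairs give 0.95 power at two-sided 0.005 for a standardised change of about 0.46 or more. Do not carry the omnibus ANOVA power over to this contrast. Its power depends on the trajectory just as the t-test's does, so that would put a new incorrect power statement in the plan. Say in the abstract which outcomes the F tests serve.

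The cost is a rewritten analysis paragraph and a few sentences on sample size. The data are already scheduled for collection and the model runs in SPSS, the software already named.
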